#### Recruitment

The subjects in this study are the HUD-VASH case managers although data about the Veterans on their caseload will also be collected. All case managers were invited to participate and consented before randomization by the study staff. The two sub-teams from each site that were assigned to GTO or IU have approximately equal numbers of case managers and vouchers, although the exact numbers shift frequently due to staff turnover and Veteran dropout, graduation, and the issuing of new vouchers. Regardless, consistent with cluster random assignment, each case manager is linked to a certain sub-team (and thus study condition), and each Veteran is in turn linked to a specific case manager. If sites decide to add new staff to a sub-team, that case manager would then automatically be assigned to the condition of that sub-team.

All HUD-VASH case managers in both groups will be invited to the webinar training on MISSION-Vet. After MISSION-Vet begins, case managers will be responsible for engaging their Veterans into MISSION-Vet services. Any Veteran participating in HUD-VASH at each of these three sites is eligible to receive MISSION-Vet services. Through training and TA, case managers and peer specialists will be guided to follow the recommended inclusion and exclusion criteria of MISSION-Vet: (1) has a current substance abuse or dependence disorder and a co-occurring mental illness and (2) is willing to participate in MISSION-Vet services. However, the decision with whom to deliver MISSION-Vet will ultimately be made by the case managers. MISSION-Vet takes about 1 year to fully deliver; therefore, Veterans will be invited to take part in MISSION-Vet in the first year of the 2-year intervention period. The study received a waiver of consent to use client-level data already being collected as part of the homeless data program management system of HUD-VASH.

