*Measures and data collection*. Each RE-AIM measure below, using data collected from aims 1–3, will be calculated for both the IU and GTO groups:*Reach*—Obtained from aim 1, the Reach measure will be the percent of all eligible Veterans who receive MISSION-Vet with adequate fidelity (defined as the endorsement of at least 75 % of the items on the MISSION-Vet Fidelity measure).*Effectiveness*—Obtained from aim 3, effectiveness will be the percentage of all eligible Veterans *who receive MISSION*-*Vet with adequate fidelity* who improve on each outcome in an amount consistent with a statistically significant effect.*Adoption*—The proportion of case managers who have more than 50 % of their eligible Veterans engaged in MISSION-Vet will be judged to have “adopted” MISSION-Vet as a standard protocol for Veterans with mental illness and co-occurring substance abuse disorders.*Implementation*—The extent to which the MISSION-Vet intervention was well implemented will come from aim 1 and be expressed as the percentage of eligible Veterans who actually participated in MISSION-Vet who had adequate fidelity (endorsement of at least 75 % of the items on the MISSION-Vet Fidelity measure).*Maintenance*—The degree to which the successful deployment of MISSION-Vet was maintained will come from data collected through the previous components of the RE-AIM model but extended a year beyond the end of the GTO support. Thus, this study will be able to assess whether MISSION-Vet maintains a high Reach, Effectiveness, Adoption, and Implementation between the end of the GTO support and the last data collection wave, which will be a year after the GTO support ends.

*Hypothesis*. We expect better results across all elements of the RE-AIM model in the GTO group than in the IU group.

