### Power analysis

We demonstrate that for aims 1, 2, and 3, we will have at least 80 % power to detect intervention effects at the 0.05 significance level (aim 4 is exploratory and thus we are not able to calculate power for that aim). Our power calculations were performed using the power analysis software G*Power 3.1.2 [49]. Previous studies examining the effect of GTO used different measures than in the current study. We therefore assumed effect sizes based on a previous study of the effect of GTO on capacity to carry out evidence-based drug abuse prevention programming. The measures used in that study were of provider knowledge (effect size = 0.21 after 2 years of GTO), attitudes (effect size = 0.38 at 1 year of GTO and 0.59 at 2 years of GTO), and skills (effect size = 0.07 at 1 year of GTO and 0.28 at 2 years of GTO) all related to the performance of practices associated with evidence-based prevention programming [16]. These measures are relevant because GTO will attempt to impact knowledge, attitudes, and skills in the proposed study as well, but in this case around the use of MISSION-Vet. We use these values as a rough guide for the effects we might expect to detect for the current study, along with conventional effect size interpretations.

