For aims 2 and 3, we will focus on the subsample of Veterans in the study for whom we have 12 months of data collected over consecutive 3-month intervals. Because these Veterans serve as their own controls relative to time, they provide the greatest power in detecting the effect of MISSION-Vet + GTO. With the same design effect as in aim 1, the effective sample size available for aims 2 and 3 controlling for clustering is 356 Veterans. For a linear repeated measures model with two treatment groups and five measurements per unit (that is, one every 3 months for a year, including baseline), and assuming a sample of 356 units to randomly divide approximately equally between the two groups, the time-by-intervention effect size that can be measured with 80 % power is 0.082. By convention, this is considered a very small effect size, and it is also small compared to the ones found above in the drug abuse prevention study. We therefore anticipate detecting effects with sufficient power for aims 2 and 3.

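### Aims 2 and 3 are called sufficiently powered because 0.082 looks small, but that figure is about a 0.41–0.46 SD arm difference, judged against provider measures and with no allowance for MISSION-Vet receipt in either arm

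*Protocol article*

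**What the plan says.** The Power analysis section claims, for Aims 1, 2 and 3 alike, "at least 80 % power to detect intervention effects at the 0.05 significance level". For Aims 2 and 3 it carries over the Aim 1 figure: "the effective sample size available for aims 2 and 3 controlling for clustering is 356 Veterans". With two groups and five measurements it reports that "the time-by-intervention effect size that can be measured with 80 % power is 0.082". It calls this very small by convention and small beside the effects of an earlier GTO study, and concludes "We therefore anticipate detecting effects with sufficient power for aims 2 and 3".

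The same section describes that benchmark: "The measures used in that study were of provider knowledge", together with attitudes and skills. The five values are 0.21 (knowledge), 0.38 and 0.59 (attitudes), and 0.07 and 0.28 (skills).

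On delivery, the Recruitment section says "All HUD-VASH case managers in both groups will be invited to the webinar training on MISSION-Vet". It requires the Veteran to be willing and leaves the choice of whom to treat to the case manager. The Overview defines IU as standard training plus access to the manuals. Aim 4 treats receipt as something to be measured and compared between arms.

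**The concern.** Two steps lie between 0.082 and the conclusion of sufficient power, and neither is sound.

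First, 0.082 is on a different scale from the values it is compared with. An interaction f for five repeated measurements is numerically much smaller than the standardised mean difference it represents. Setting it beside effects of 0.07 to 0.59, or beside the 0.2 and 0.5 conventions used for Aim 1, makes the detectable effect look smaller than it is. The benchmarks are also staff outcomes, whereas Aims 2 and 3 concern Veterans' housing, symptoms and functioning.

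Second, GTO supports staff. In a comparison of all Veterans served, it moves Veteran outcomes mainly through more, or better, MISSION-Vet in the GTO arm than in the IU arm. The net contrast is then roughly the MISSION-Vet effect in recipients times the between-arm difference in effective receipt. The article foresees incomplete receipt and offers MISSION-Vet in both arms, yet judges the plausibility of its detectable effect without considering either.

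At stake is the reading of a null result. With an unqualified claim of at least 80 % power, a non-significant housing or symptom comparison could be taken as evidence that GTO or MISSION-Vet does not help.

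**Working it through.** **Inputs from the article.** 2110 vouchers, reduced by 20 % and then 5 %; 66 case managers; ICC 0.15; two groups; five measurements; alpha 0.05; power 80 %; "Our power calculations were performed using the power analysis software G*Power 3.1.2"; medium effect 0.5.

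**Assumed, because the article does not state them.** Within-Veteran correlation ρ, shape of the arm divergence, effect in recipients, and receipt in each arm.

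**1. Reproduce the plan's figures.**
- 2110 × 0.80 × 0.95 = 1603.6, taken as 1604.
- m = 1604/66 = 24.3; Deff = 1 + 23.3 × 0.15 = 4.495; 1604/4.495 = 356.8, taken as 356.
- Within-between interaction F test: λ = f² × N × 5/(1 − ρ), df 4 and 1416. With f = 0.082, N = 356 and ρ = 0, λ = 0.006724 × 1780 = 11.97 and power is 79.98 %.
- Other correlations do not return 0.082: the detectable f is 0.071 at ρ = 0.25, 0.058 at 0.5 and 0.045 at 0.7. So ρ = 0 is inferred.

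The figure 0.082 is therefore correctly calculated on those settings.

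**2. Put 0.082 on the SD scale.** For an arm difference D at month 12 with time profile p, f = (D/2) × √mean[(p − p̄)²].
- Linear divergence, p = 0, 0.25, 0.5, 0.75, 1: √0.125 = 0.3536, so f = 0.1768 D and D = 0.082/0.1768 = 0.46.
- Step from month 3, p = 0, 1, 1, 1, 1: √0.16 = 0.4, so f = 0.2 D and D = 0.082/0.2 = 0.41.

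On this scale 0.41–0.46 exceeds 0.07, 0.21, 0.28 and 0.38. Only 0.59 is larger.

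**3. MISSION-Vet effect required for 80 % power.** This is D divided by the GTO–IU difference in receipt (step–linear, in SD).

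| Receipt difference | ρ = 0 | ρ = 0.5 | ρ = 0.7 |
|---|---|---|---|
| 100 points | 0.41–0.46 | 0.29–0.33 | 0.22–0.25 |
| 50 points | 0.82–0.93 | 0.58–0.66 | 0.45–0.51 |
| 25 points | 1.64–1.86 | 1.16–1.31 | 0.90–1.02 |

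**4. Power for an assumed 0.5 SD effect in recipients.** D = 0.5 × receipt difference, N = 356. Example at 50 points and ρ = 0: D = 0.25. Linear f = 0.0442, λ = 3.48, power 27.9 %. Step f = 0.050, λ = 4.45, power 35.3 %.

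| Receipt difference | ρ = 0 | ρ = 0.5 | ρ = 0.7 |
|---|---|---|---|
| 100 points | 86–94 % | over 99 % | over 99 % |
| 75 points | 59–72 % | 90–96 % | over 99 % |
| 50 points | 28–35 % | 53–66 % | 79–89 % |
| 25 points | 10–11 % | 15–19 % | 24–30 % |

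Only the difference matters in this approximation: 75 % against 25 % gives the same power as 50 % against 0 %.

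**The case against.** **Nothing is miscalculated, and a detectable GTO–IU effect is a net effect that already contains whatever uptake occurs.** This stands. The number 0.082 needs no uptake multiplier. What fails is the inference from it to sufficient power, which is a judgement about plausible effects and has to take receipt into account.

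**The correlation is back-solved.** This also stands. The article says Veterans act as their own controls, which fits poorly with zero correlation. At 0.7, the 50-point scenario reaches about 80 %. No single power figure is defensible, so a range is given.

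**The Aim 2 hypothesis is worded for Veterans who receive MISSION-Vet in both arms.** On that reading the dilution does not apply in this form. At 50 % uptake in both arms there would be 802 Veterans, m = 12.2, Deff = 2.67, effective N = 300 and detectable f = 0.089. But the data source for Aims 2 and 3 is all Veterans served, and the power calculation keeps the full 356. Recipients are also chosen by case managers after randomisation. The wording leaves an ambiguity to resolve and does not support the claim as printed.

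**A Hybrid Type III trial puts the implementation strategy first, and the Discussion calls effectiveness secondary.** True, but the Power analysis section still gives Aims 2 and 3 the same assurance as Aim 1.

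A reader might also infer that the plan expects 50 % uptake, since Aim 4 says "The proportion of case managers who have more than 50 % of their eligible Veterans engaged in MISSION-Vet will be judged to have" adopted it, and so that its own figures leave 28–35 % power. The article does not support that. The 50 % is a cut-off for classifying a case manager, not an expected uptake or a between-arm difference, and 28–35 % also needs zero correlation.

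**Conclusion.** The point holds as a criticism of the conclusion, not of the arithmetic. On the zero correlation that reproduces it, 0.082 is an arm difference of 0.41–0.46 SD at month 12. That is close to the article's medium effect and, if the cited effects are standardised mean differences, larger than four of the five. The article offers no Veteran-level evidence that a net difference of this size is plausible, and it does not weigh discretionary delivery or IU receipt.

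The loss of power cannot be fixed at one value, because expected uptake is not given. For 0.5 SD in recipients, it ranges from 28–35 % (ρ = 0) to 79–89 % (ρ = 0.7) at a 50-point receipt difference, and from 10–11 % to 24–30 % at 25 points. These figures rest on an all-Veterans comparison, an effective N of 356 taken at face value, the four-degree-of-freedom interaction test, and GTO acting through MISSION-Vet receipt.

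It would go too far to say that 80 % power needs nearly every GTO Veteran and almost no IU Veteran to be treated. At ρ = 0 and a 0.8 SD effect, a difference of 51–58 points suffices (0.41/0.8 to 0.464/0.8). At ρ = 0.5 and 0.5 SD, 58–66 points suffices (0.29/0.5 to 0.328/0.5).

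**What to change.** 1. Withdraw the unconditional statement that Aims 2 and 3 have sufficient power.
2. Restate the detectable effect as a GTO–IU difference in SD units, and state the within-Veteran correlation and divergence shape assumed.
3. Show the MISSION-Vet effect this requires: the detectable arm-level difference divided by the assumed GTO–IU difference in receipt, for several receipt differences and correlations, as in the first table above.
4. Stop using the provider knowledge, attitude and skill effects as the yardstick for Veteran outcomes.
5. State that the Aim 2 and 3 comparison uses all eligible Veterans served, and reconcile the Aim 2 hypothesis wording with its data source. Do not restrict the comparison to recipients to recover power.
6. Report Aims 2 and 3 as estimates with confidence intervals, and say that a non-significant result is not evidence of no effect unless the interval excludes a meaningful difference.

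This changes wording and a short calculation only. It needs no extra Veterans or data. The price is a less favourable power statement for the Veteran outcomes.

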### Design challenges

An important design issue is whether to randomize at the site, provider, or Veteran level. We decided to randomize at the HUD-VASH case manager level for several reasons. First, the analysis of national HUD-VASH data showed that the HUD-VASH site was the strongest predictor of housing stability [6]. Therefore, it was important to hold the site constant by having IU and GTO conditions equally represented within each of the sites. Further, we account for the effects of case manager clustering in our statistical analyses. Second, we believe that the possible contamination that may result between IU and GTO conditions being present at the same site is manageable. In the past studies of GTO, contamination did occur but was moderate (across multiple programs, mean = 0.5 to 1.0 on a 6-point index of possible GTO activities in which one could engage) [16]. We have however, purposely selected large sites in an effort to minimize the contamination as it is believed that we can minimize discussion of GTO implementation strategies more easily among non-GTO case managers in larger sites. To minimize contamination further given its potential confound, we decided to use naturally occurring HUD-VASH sub-teams at each site so that team meetings and other routine discussions between case managers are handled in separate IU and GTO “teamlets.” Other limitations of the study include staff turnover and changes in policy directives. Regarding staff turnover, we anticipate some level of turnover, and our power analyses show that we have a sufficient sample. Furthermore, new staff in the IU sites will receive training on MISSION-Vet. As for changes in the program directives, we acknowledge that this is also a limitation as there is always ongoing tension between research and the need for patient care services to make and respond to new directives to end homelessness. However, our design—comparing an organizational intervention like GTO to usual implementation strategies (regardless of how they may change)—is therefore a genuine test of the impact of the GTO intervention (and MISSION-Vet as well) in real-world conditions. Thus, the findings that are produced may have greater ecological validity—or relevance to real world conditions, where circumstances do change. In addition, even if the VA did make changes to HUD-VASH, the changes would apply evenly to all HUD-VASH sites and all HUD-VASH case managers and thus be equal across IU and GTO conditions. Further, we would hypothesize that GTO would be able to help HUD-VASH case managers incorporate the changes for improved Veteran impact better than case managers assigned to the IU condition.

### Trial status

Central IRB approval for this study was granted in October of 2011. The three sites were trained on MISSION-Vet and GTO in the first half of 2013. The first GTO planning meetings began directly after training occurred, between January 2013 and November 2013 across the three sites. The data collection—via a fidelity measure embedded into the VA Electronic Medical Record System—began as each site initiated MISSION-Vet, between April 2013 and January 2014.

## Discussion

As noted above, research evidence and passive dissemination strategies often do not change clinical practice or increase the adoption of new practices. MISSION-Vet has demonstrated evidence, yet has not been widely adopted despite encouragement from the VA nationally. This project intends to test whether a comprehensive implementation strategy—Getting To Outcomes—can aid in MISSION-Vet’s implementation in HUD-VASH and secondarily to evaluate the effectiveness of the MISSION-Vet treatment. Further, this project will yield important lessons about *how* and *under what conditions* GTO support aids MISSION-Vet implementation. The test will be challenging as HUD-VASH teams are under increasing pressure to focus on housing placement to meet Obama’s administration pledge to end homelessness. However, the case managers randomized to receive GTO will have a number of additional supports to assist with the implementation of the MISSION-Vet model within HUD-VASH. If successful, GTO could be used as a model to more widely support MISSION-Vet implementation or the implementation of other evidence-based practices. In addition, study results will continue to evaluate the efficacy of MISSION-Vet for the treatment of homeless Veterans with co-occurring disorders.

This project is registered at ClinicalTrials.gov with number NCT01430741 (URL: https://clinicaltrials.gov/ct2/show/study/NCT01430741?term=sdp+11-240&rank=1).

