**Methods/design:**

In three large VA Medical Centers, this Hybrid Type III trial will randomize case managers and their clients by HUD-VASH sub-teams to receive either MISSION-Vet Implementation as Usual (IU—standard training and access to the MISSION-Vet treatment manuals) or MISSION-Vet implementation augmented by GTO. In addition to testing GTO, effectiveness of the treatment (MISSION-Vet) will be assessed using existing Veteran-level data from the HUD-VASH data monitoring system. This project will compare GTO and IU case managers and their clients on the following variables: (1) fidelity to the MISSION-Vet intervention; (2) proportion of time the Veteran is housed; (3) mental health, substance use, and functional outcomes among Veterans; and (4) factors key to the successful deployment of a new treatment as specified by the Reach, Effectiveness, Adoption, Implementation, and Maintenance (RE-AIM) model.

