**Discussion:**

This project is an important step for developing an implementation strategy to increase adoption of evidence-based practice use in VA homeless programs, and to further examine efficacy of MISSION-Vet in HUD-VASH. This project has important implications for program managers, policy makers, and researchers within the homelessness field. VA Central IRB approval for this study was granted in October 2011. The three sites were trained on MISSION-Vet and GTO in the first half of 2013. The first GTO planning meetings began after training occurred, between January 2013 and November 2013, across the three sites. The data collection—via a fidelity measure embedded into the VA Computerized Patient Record System—began as each site initiated MISSION-Vet, between April 2013 and January 2014.

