## Methods

### Overview

This project is a Hybrid Type III, cluster randomized controlled trial [19] that compares MISSION-Vet Implementation as Usual (IU—standard training and access to the MISSION-Vet treatment manuals) to MISSION-Vet implementation augmented by GTO. This study is being carried out in HUD-VASH teams at three large VA Medical Centers over a 2-year period. Within each site, existing sub-teams (case managers and Veterans they serve) are the clusters that will be randomly assigned, which is particularly appropriate when desiring to lessen the risk of experimental contamination [20] of the implementation strategy. Blinding in the traditional sense—e.g., data collectors blinded to subjects’ treatment assignment—will not be possible; however, all data will be coming from secondary sources. As a Hybrid Type III trial, it will emphasize the test of an implementation strategy (GTO), while using VA’s existing HUD-VASH data monitoring system to also assess the effectiveness of the treatment (MISSION-Vet) [21] called *HOMES* (Homeless Operations, Management and Evaluation System). This design is appropriate when the implementation strategy has strong preliminary evidence, the EBP in question has solid evidence but could yield weaker outcomes in new or less controlled environments than was present in efficacy trials, and the EBP has “implementation momentum” [21]. These conditions are present for implementing MISSION-Vet in HUD-VASH, as will be shown below. The trial assesses three sets of variables: a) MISSION-Vet implementation (adoption, dose, reach, fidelity), b) outcomes among HUD-VASH Veterans (mental health and substance use, community functioning, housing), and c) MISSION-Vet implementation barriers and facilitators organized by the CFIR.

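### Neither the GTO versus IU contrast nor any analysis described in Aims 1–4 isolates the effect of MISSION-Vet, so the claims to assess its effectiveness or efficacy are not supported

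*Protocol article*

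**What the plan says.** **The arms.** The Overview states that the trial "compares MISSION-Vet Implementation as Usual (IU—standard training and access to the MISSION-Vet treatment manuals) to MISSION-Vet implementation augmented by GTO". Under Recruitment, "All HUD-VASH case managers in both groups will be invited to the webinar training on MISSION-Vet". The same section leaves delivery to the case manager: "However, the decision with whom to deliver MISSION-Vet will ultimately be made by the case managers".

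**The claims about MISSION-Vet itself.**
- Abstract, Methods/design: "effectiveness of the treatment (MISSION-Vet) will be assessed using existing Veteran-level data from the HUD-VASH data monitoring system".
- Abstract, Discussion: the project is a step "to further examine efficacy of MISSION-Vet in HUD-VASH".
- Overview: repeats that the treatment's effectiveness is also assessed, from HOMES data.
- Design challenges: comparing GTO with usual implementation is called "a genuine test of the impact of the GTO intervention (and MISSION-Vet as well) in real-world conditions".
- Discussion: names evaluation of MISSION-Vet's effectiveness as a secondary purpose, and closes with "study results will continue to evaluate the efficacy of MISSION-Vet for the treatment of homeless Veterans with co-occurring disorders".

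**The concern.** A treatment's effect is identified by comparing people offered or given it with comparable people who are not. No such comparison is set up here: MISSION-Vet is available on both sides of the randomisation, and the randomised difference is the implementation support.

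What is at stake is the conclusion drawn from Aims 2 and 3. The Background treats MISSION-Vet's success in HUD-VASH as an open question, and the Abstract addresses the results to program managers and policy makers. If the article tells them that the treatment was evaluated, a null difference may be read as MISSION-Vet failing in this setting, and a positive one as MISSION-Vet working. The contrast supports neither reading.

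**Working it through.** The claim has no figure of its own to reproduce, so the check sets each described analysis beside the claim and then writes out what the contrast contains.

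**Analyses described**

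| Analysis | What is compared | Comparator without MISSION-Vet? |
|---|---|---|
| Aim 1, fidelity | GTO vs IU | No |
| Aim 2, days housed | Hypothesis: recipients under GTO vs recipients under IU | No; receipt is common to both sides |
| Aim 3, mental health, substance use, functioning | Hypothesis: GTO Veterans who received MISSION-Vet vs Veterans of IU case managers | No; read literally, it mixes GTO support, receipt and selection of recipients |
| Aim 4, Effectiveness | Percentage improving among adequate-fidelity recipients, calculated in each arm; t tests of mean scores at the end of GTO support | No |
| Other Aim 4 measures | Proportions, GTO vs IU | No |

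The Power analysis follows the same contrast. The detectable 0.298 is for the Aim 1 fidelity score between arms. The 0.082 for Aims 2 and 3 is a time-by-intervention effect, again between arms.

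**What the contrast contains.** Let p_G and p_I be the proportions of Veterans receiving MISSION-Vet in each arm, δ the effect of receiving it (fidelity taken as equal), and γ any effect of GTO on Veterans by other routes. The expected difference between arms is

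D = δ(p_G − p_I) + γ.

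- If p_G = p_I and γ = 0, then D = 0 whatever δ is. A null fits an effective MISSION-Vet.
- If D > 0, then δ = 0 with γ = D fits as well as γ = 0 with δ = D/(p_G − p_I). Uptake can be observed, but δ and γ are two unknowns in one equation.

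The article does not rule out γ. Design challenges itself expects GTO to help case managers absorb changes in program directives to Veterans' benefit. That route need not pass through MISSION-Vet.

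**Non-randomised routes**
- *Recipients against non-recipients.* Case managers choose recipients, guided by diagnosis and willingness, so the groups differ by selection.
- *Change within Veterans.* The Power analysis says that Veterans act as their own controls over time, but the quantity it powers is time-by-intervention. Change alone would also include the effects of the voucher, standard case management and the other services that about 75% of these Veterans receive (Site composition).
- *Arm as an instrument for uptake.* This would need γ = 0 and p_G different from p_I. No such analysis is described.

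**The case against.** **Hybrid Type III.** The strongest defence is that the label announces a test of the implementation strategy with treatment outcomes collected alongside. Assessing or evaluating a treatment need not promise a randomised estimate, and only Design challenges uses the word test for MISSION-Vet. It is true that collecting Veteran outcomes is legitimate and that the wording varies in strength. But the label does not change what two arms identify, and the word efficacy appears in both the Abstract and the Discussion. The Aim 2 and Aim 3 headings already name GTO and IU correctly, which is why the MISSION-Vet claims elsewhere conflict with them.

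**Stronger readings that the article does not support**
- *Every Veteran in both arms receives MISSION-Vet.* Delivery is elective, and the Aim 1 data cover all HUD-VASH Veterans of case managers in both conditions, so non-recipients are in the data. Uptake may well differ by arm; that is the premise of testing GTO.
- *Nothing about MISSION-Vet can be learned from these data.* Observational or instrumental estimates are conceivable. They are not described, and they would rest on assumptions that the design does not secure.
- *Any effect through MISSION-Vet would fall below the detectable 0.298.* That figure belongs to Aim 1 fidelity. Aims 2 and 3 state 0.082 on a different scale, and any effect or uptake gap put into the formula would be an assumption.

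**Hypothetical harm.** It is also fair to say that no sentence commits the authors to misreading a null. The harm is a foreseeable misreading, not a planned one. The phrase MISSION-Vet + GTO in the Power analysis is minor: it describes what the GTO arm gets, though not what separates the arms.

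**Conclusion.** The point holds in this form: neither the randomised GTO versus IU contrast nor any analysis described in Aims 1–4 isolates the effect of MISSION-Vet. The statements in the Abstract (Methods/design and Discussion), Overview, Design challenges and Discussion that its effectiveness or efficacy is assessed or tested therefore go beyond the design.

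This rests only on the article's own description of the arms, of who chooses recipients and of the analyses; no assumed number is needed. There is no defensible magnitude to attach. The randomisation, endpoints, models and power figures are unaffected by this point. What changes is what the trial may conclude, so the correction should be made, although it is one of wording.

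**What to change.** 1. State that Aims 2 and 3 estimate the effect on Veteran outcomes of adding GTO to MISSION-Vet implementation.
2. Remove or qualify the claims about MISSION-Vet's own effectiveness or efficacy in all five places: Abstract Methods/design, Abstract Discussion, Overview, Design challenges (the words in parentheses) and Discussion. Leaving out the Overview would leave the claim standing in the Methods.
3. Label any analysis of change within Veterans, of recipients against non-recipients, or of fidelity against outcome as observational.
4. State that a null GTO versus IU result is not evidence against MISSION-Vet, and that a positive one may include direct effects of GTO.

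The cost is wording and a narrower claim. No data collection, sample size or model changes.
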